## Abstract

In resource-rich countries, almost all severe hemophilia patients receive prophylactic replacement therapy with factor concentrates to prevent spontaneous bleeding in joints and muscles to decrease the development of arthropathy and risk of long-term disability. Pharmacokinetic (PK)-guided dosing can be applied to individualize factor replacement therapy, as interindividual differences in PK parameters influence factor VIII (FVIII) and FIX activity levels. PK-guided dosing may therefore lead to more optimal safeguarding of FVIII/FIX levels during prophylaxis and on demand treatment. The OPTI-CLOT TARGET study is a multicenter, nonrandomized, prospective cohort study that aims to investigate the reliability and feasibility of PK-guided prophylactic dosing of factor concentrates in hemophilia-A and -B patients in daily clinical practice. At least 50 patients of all ages on prophylactic treatment using standard half-life (SHL) and extended half-life (EHL) factor concentrates will be included during 9 months and will receive PK-guided treatment. As primary endpoint, a minimum of four FVIII/FIX levels will be compared with FVIII/FIX levels as predicted by Bayesian forecasting. Secondary endpoints are the association of FVIII and FIX levels with bleeding episodes and physical activity, expectations and experiences, economic analyses, and optimization of population PK models. This study will lead to more insight in the reliability and feasibility of PK-guided dosing in hemophilia patients. Moreover, it will contribute to personalization of treatment by greater knowledge of dosing regimens needed to prevent and treat bleeding in the individual patient and provide evidence to more clearly associate factor activity levels with bleeding risk.

## Introduction

Hemophilia A and hemophilia B are X-linked recessive bleeding disorders caused by a deficiency or dysfunction of coagulation factor VIII (FVIII) or FIX, respectively. Severe patients (FVIII/FIX < 0.01 IU/mL) and some moderate-to-severe patients (FVIII/FIX: 0.01–0.05 IU/mL) suffer from spontaneous bleeding or bleeding after minimal trauma. Prophylactic treatment by intravenous administration of factor concentrates aims to prevent (spontaneous) bleedings in joint and muscles and subsequent arthropathy with potential long-term disability.
1
2

During prophylaxis theoretically, FVIII/FIX trough levels is targeted to >0.01 IU/mL. This principle is based on observations by Ahlberg as early as in 1965 that bleeding phenotype and joint status are strikingly different between severe and moderate-to-severe hemophilia patients with only minimal baseline FVIII level differences (<0.01 vs. 0.01–0.05 IU/mL).
3
To achieve these FVIII/FIX trough levels during prophylaxis, FVIII/FIX concentrates are mostly prescribed according to body weight.
2
Remarkably, it is still not usual clinical practice to standardly measure and monitor trough FVIII/FIX levels when no bleeding occurs. To personalize dosing, information on trough FVIII/FIX levels is of value to establish if prophylaxis is adequate for each individual patient, during follow–up, and in varying circumstances and when dosing on demand. In addition, the lack of knowledge of achieved FVIII/FIX levels impedes proper switching to novel long-acting factor concentrates due to uncertainties which trough FVIII/FIX target levels should be targeted to prolongate earlier effective prophylactic treatment to prevent bleeding, especially in relation to physical activity or sports.

### Pharmacokinetic-Guided Dosing

Large interindividual variability exists in the pharmacokinetics (PKs) of FVIII/FIX concentrates as demonstrated by Björkman et al among others.
4
5
6
To understand and predict the consequences of the interindividual variability of factor concentrates in individuals, population PK models have been constructed for prophylaxis
4
7
8
9
10
11
12
13
14
15
16
17
18
19
20
21
22
23
24
25
26
27
28
29
30
31
32
and perioperative treatment
33
with standard half-life (SHL) and extended half-life (EHL) FVIII and FIX concentrates for hemophilia-A and -B patients, respectively. With these population PK models, Bayesian forecasting can be performed. Herewith, individual PK parameters are estimated which are subsequently used to calculate the adequate dose for an individual patient to achieve FVIII/FIX target levels, both trough and peak. The availability of population PK models has made limited sampling possible, making prior frequent blood sampling (>10 blood samples)
34
and a wash-out period redundant. PK-guided dosing has also been reported to not only be able to predict dosing requirements to attain certain target FVIII/FIX levels but also to decrease the amount of factor concentrates with concomitant reduction of costs.
33
Carlsson et al was the first to report a dose and cost reduction of 30% of FVIII concentrate without an increase in bleeding events, when PK-guided prophylactic dosing was compared with standard prophylactic dosing in a small patient sample.
35
However, a recent randomized controlled perioperative trial was not able to show a decrease in FVIII concentrate consumption, although achievement of FVIII target ranges was clearly more optimal.
36

We hypothesize PK-guided dosing leads to individualization of prophylaxis which is in accordance with the recommendations of the subcommittee on FVIII, FIX, and rare bleeding disorders of the International Society on Thrombosis and Haemostasis (ISTH).
37
PK-guided dosing may help achieve higher trough levels more efficiently when clinically indicated, as well as provide guidance when patients switch to alternative replacement factor concentrates, while taking cost and benefit of treatment into account. In addition, PK-guided dosing may lead to increased insight into the association between FVIII/FIX levels, bleeding (risk), and physical activity levels in individual patients as factor levels can be predicted at any time point and related to bleeding and activity. Therefore, we aim to prove that FVIII/FIX trough and peak levels as set by treating physician can be predicted and achieved reliably by application of PK-guided prophylaxis and that this intervention is feasible for patients and treatment teams.

## Objective

Investigate the reliability and feasibility of PK-guided prophylactic dosing of factor concentrates in hemophilia-A and -B patients in daily clinical practice.

## Methods

### Study Design

The OPTICLOT TARGET study is a multicenter, nonrandomized, prospective cohort study.

### Study Population

Patients will be recruited from the two Dutch Hemophilia treatment Centers; follows Erasmus MC, University Medical Center Rotterdam and Amsterdam University Medical Centers.

#### Inclusion Criteria

Inclusion criteria are as follows:

Hemophilia-A and -B patients of all ages on prophylaxis.Prophylaxis with SHL or EHL factor concentrates.Written (parental) informed consent, according to local law and regulations.

#### Exclusion Criteria

Exclusion criteria are listed below:

Patients with other severe congenital or acquired hemostatic abnormalities.General medical conditions which may interfere with participation in the study.Inability to adhere to prophylaxis and/or inability to keep detailed logs on infusion and bleeding episodes.Withdrawal of (parental) informed consent.Presence of FVIII/FIX inhibitor, leading to alternative treatment with bypassing products, immune toleration induction, and/or other immune modulating treatment.

### Outcome Measures

#### Primary Endpoints

Observed FVIII and FIX levels in comparison to FVIII and FIX levels are predicted by Bayesian forecasting. The predictive performance is deemed acceptable when at least 80% of the actual FVIII/FIX levels are within ± 25% of the predicted (target) values as stated by treating professional.

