**Fig. 2 FI210067-2:**
[figure not shown]
Time points (T) of laboratory tests during individual PK-profiling. A preinfusion,
*t*
 = 15–30 minutes and t = 4 hours sample (left) are performed in all patients. The other time points (right) depend on hemophilia type and brand of factor concentrate. EHL, extended half-life; PK, pharmacokinetic; SHL, standard half-life.

Dosing will be advised by clinical pharmacologist on the basis of FVIII/FIX target trough levels as set by treating physician, in accordance to patient characteristics, previous trough levels (if a patient switches between factor concentrates), bleeding history, activity pattern, and in consultation with patient/caretakers. If desirable, physicians are also able to set FVIII/FIX target peak levels during intensive physical activities. In this way, treatment is truly customized and tailored to the needs and lifestyle of each individual as personalization is meant to be. Retrospective data of a patient, such as previous trough levels and factor levels at onset of a bleed or during sport activities, can be informative to the physician to set target levels.

Thereafter, patients will initially be on PK-guided treatment for 12 weeks. During these 12 weeks, a minimum of three factor levels will be measured and compared with predicted FVIII/FIX values to validate predicted dosing regimen (
Table 3
). Patients on EHL will be on iterative PK-guided treatment with dose adjustment if needed based on both factor levels and bleedings. Iterative treatment is desirable in these patients as most patients initiate treatment with EHL factor concentrates after being on prophylaxis with SHL factor concentrates. Because of the lack of knowledge of most optimal (frequency and dose of) EHL factor concentrate, this period has a dose finding perspective.

For patients on SHL predicted FVIII/FIX values will be blinded to the treating physician and dosages will not be adjusted during the first 10 weeks. Thereafter, dose adjustment can be made.

A subsequent follow-up period of 24 weeks on PK-guided treatment is necessary to further collect data to establish the associations between FVIII/FIX levels and bleeding events. Only if clinically indicated, FVIII/FIX levels will be measured during bleeds (
Table 3
). At the end of this follow-up period, one final blood sample will be taken to compare the factor level with the predicted value (
Table 3

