### Statistical Analysis

Continuous data will be expressed as mean and standard deviation when normally distributed or median and interquartile range when not normally distributed. Categorical data will be expressed as frequency and percentage.

As described in the primary study endpoint, the predictive performance of PK-guided dosing is deemed acceptable when at least 80% of the actual FVIII/FIX levels are within ± 25% of the predicted (target) values as stated by treating professional. Both the mean error between the predicted and observed factor level and the mean absolute difference of the predicted level will be calculated. No significant bias presented as zero is included in the 95% confidence interval (CI) of the mean error. Moreover, differences between the predictive performance of different factor concentrates and age groups will be investigated and described.

Association of factor levels with bleedings will be described according to sub classifications. Comparisons of the ABR and joint status before and during PK-guidance will be analyzed using a paired
*t*
-test or Wilcoxon's test, depending on the distribution.

R (version 4.0.3) will be used for statistical analysis.

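### The 80% within ±25% rule suits forecast accuracy, but it has no direction and cannot by itself show that the physician's trough targets were achieved

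*Protocol article*

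**What the plan says.** The aim at the end of the Pharmacokinetic-Guided Dosing section has two parts: that "FVIII/FIX trough and peak levels as set by treating physician can be predicted and achieved reliably". Under Interventions, dosing is advised "on the basis of FVIII/FIX target trough levels as set by treating physician", with peak targets optional.

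Primary Endpoints first names a forecast comparison ("Observed FVIII and FIX levels in comparison to FVIII and FIX levels are predicted by Bayesian forecasting") and then fixes the acceptance rule: "at least 80% of the actual FVIII/FIX levels are within ± 25% of the predicted (target) values as stated by treating professional". Statistical Analysis repeats the rule and adds two summaries: "Both the mean error between the predicted and observed factor level and the mean absolute difference of the predicted level will be calculated". A bias criterion follows: "No significant bias presented as zero is included in the 95% confidence interval (CI) of the mean error".

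As background, the Introduction describes the usual trough target as a lower limit: "During prophylaxis theoretically, FVIII/FIX trough levels is targeted to >0.01 IU/mL".

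**The concern.** A treating professional states targets; the Bayesian model produces forecasts. By setting the two side by side as one reference value, the rule is made to serve for prediction and for attainment at once. A symmetric window is natural for prediction, because error in either direction is error. For attainment of a trough level, a shortfall and an excess do not mean the same thing, and the rule treats them alike.

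The article names no figure that counts trough samples at or above the set target. If the 80% rule is met, a report could therefore say that targets were achieved when the data show only that levels lay near them, possibly mostly below.

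**Working it through.** **Inputs from the Protocol article.** Window ±25% and threshold 80% (Primary Endpoints); at least 50 patients (Sample Size Calculation); at least four levels per patient (Abstract), so at least 50 × 4 = 200 levels. There is no stated power or precision figure to reproduce.

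**Assumptions.** The article gives no spread or bias for the prediction error. Log SDs of 0.10 and 0.15 are assumed, with the forecast equal to the trough target and samples taken at trough.

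**1. Direct reading of the window.** For a target of 0.010 IU/mL the window is 0.0075 to 0.0125. A trough of 0.0076 (24% under) counts as a hit; one of 0.0130 (30% over) counts as a miss.

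**2. The rule alone, log-normal ratios.** Let m be the median observed/target ratio and s the log SD.
- Share in window = Φ((ln 1.25 − ln m)/s) − Φ((ln 0.75 − ln m)/s), with ln 1.25 = 0.223 and ln 0.75 = −0.288.
- Share below target = Φ(−ln m/s).

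| s | m | Share in window | Share below target |
|---|---|---|---|
| 0.15 | 0.90 | Φ(2.19) − Φ(−1.21) = 87.4% | Φ(0.70) = 76% |
| 0.10 | 0.85 | Φ(3.86) − Φ(−1.25) = 89.5% | Φ(1.63) = 95% |

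**3. Same check with normal relative errors.** Let b be the bias and s the SD. Share in window = Φ((0.25 − b)/s) − Φ((−0.25 − b)/s); share below = Φ(−b/s). The chance of meeting the rule is the binomial probability of at least 160 of 200 independent levels in the window.

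| s | b | In window | Below target | Chance rule met |
|---|---|---|---|---|
| 10% | −10% | 93.3% | 84.1% | about 1.00 |
| 10% | −15% | 84.1% | 93.3% | 0.95 |
| 15% | −10% | 83.2% | 74.8% | 0.90 |
| 20% | 0 | 78.9% | 50.0% | 0.39 |

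So the point matters when the spread is small enough for the rule to be met at all.

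**4. Does the planned bias check catch this?** On a relative scale, yes for a uniform shift. In the first three rows above, the 95% CI of the mean error excludes zero with probability at least 0.997, whether n is 200 (independent levels) or 50 (the fully clustered bound).

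It has three limits:
- *No link.* Nothing in Statistical Analysis says that a significant bias overrides an 80% rule that has been met.
- *Scale and pooling.* The error is written as a difference between levels. Suppose 150 troughs (target 0.02 IU/mL, bias −15%, SD 10%) are pooled with 50 unbiased peaks (0.80 IU/mL, SD 12%), all assumed. The mean error is (150/200) × 0.02 × (−0.15) = −0.00225 IU/mL. One peak has SD 0.80 × 0.12 = 0.096, and the standard error of the pooled mean is about 0.0034. The ratio is about 0.66, far short of 1.96. In simulation the 80% rule was met in 99.9% of trials, bias was flagged in about 11%, and 93% of troughs were below target.
- *Zero mean error is not attainment.* With a median ratio of 1, half of the troughs lie below target whatever the spread. A skewed set of 160 levels at −10% and 40 at +40% has mean error 0 (95% CI about −2.8% to +2.8%), exactly 80% in the window and 80% below target.

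**The case against.** The strongest reply is that direction is analysed: the signed mean error and its confidence interval follow directly after the repeated rule. That stands. A reader might infer that the plan is blind to a systematic shortfall, but the article does not support this, and step 4 shows that a uniform relative shift would almost surely be seen.

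It also stands that a two-sided window fits the endpoint named, which is predictive performance. Excess is not free either, since the article cites concentrate use and cost and plans an economic analysis. The lower-limit wording in the Introduction is general background and does not make every physician-set target a strict floor.

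Three further inferences should not be drawn.
- *That the rule rejects good dosing that runs high.* Under the log-normal model, levels 10% high (log SD 0.15) or 15% high (log SD 0.10) give 79.8% in the window. That is 0.2 points short, and with 200 independent levels the rule would still be met about 51% of the time. Under normal relative errors, high and low shifts of equal size give the same share.
- *That ±25% should become a ratio-symmetric window such as 0.80 to 1.25.* That is a convention, and ±25% is not an error.
- *That half of troughs below target is a failing.* It follows from any unbiased forecast with doses aimed at the target.

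Finally, Table 3 does not say that the samples are troughs, and a level under forecast is under target only where the two coincide. The figures above depend on both conditions.

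**Conclusion.** The concern holds in a limited form. The rule is a fair test of prediction, but its wording lets it stand for attainment too, and for that it is not enough. Under the assumed log-normal errors (log SD 0.10 to 0.15, shift of 10% to 15% low) it is met with 76% to 95% of troughs below target. The normal model gives 75% to 93%. The bias criterion narrows the gap without closing it, for the three reasons in step 4. The article states the acceptance rule twice, so this concerns what is fixed there rather than detail left to a fuller document. The size depends wholly on assumed spread and bias, on forecasts equal to targets, and on sampling at trough.

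**What to change.** 1. Keep the ±25% rule as the test of prediction, and name forecast and physician's target as separate comparators.
2. State that performance is acceptable only if the bias criterion is also met, with the error on a relative scale and computed separately for troughs and peaks.
3. For trough samples where a trough target was set, report the share at or above that target, with a confidence interval that allows for several levels per patient. Report the misses below and above the window separately. The share is descriptive and needs no pass mark, because about half of levels fall below target even when forecasts are unbiased.
4. Do not rest a claim that targets were achieved on the 80% rule alone.

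This uses samples already planned in Table 3. The cost is a little more analysis and possibly a less favourable statement on attainment.

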#### Secondary Endpoints

The four secondary endpoints are briefed below:

Association of (real world or predicted) FVIII/FIX levels with bleeding episodes and daily activities. Additionally, bleeds will be categorized according to the following subclassifications: total number of bleeds over time, number of spontaneous bleeds, number of traumatic bleeds, number of joint bleeds, number of target joint bleeds, and bleed severity.Expectations, feasibility, and experience with PK-guided dosing with the different factor concentrates (SHL vs. EHL) as reported by patient/caretakers and physician will be measured using a visual analogue scale (VAS) questionnaire at the start and end of the study.Economic analysis in which costs and benefits of standard prophylactic treatment and PK-guided prophylaxis are compared.Analysis of described modifiers effecting PK parameters of FVIII/FIX concentrate to further optimize population PK models. Modifiers include demographics (such as lean body mass) and laboratory measurements (such as the von Willebrand Factor levels).

### Interventions

Study interventions are depicted in the flowchart (
Fig. 1
). Patients will be categorized into strata according to type of hemophilia and type of factor concentrate (SHL or EHL). For all patients, the following patient characteristics and demographics will be collected: type of hemophilia, endogenous factor level, DNA mutation, age, height (cm), weight (kg), body mass index (BMI; kg/cm
^2^
), lean body mass (kg), blood group, current other medication, and activity patterns.

**Fig. 1 FI210067-1:**
[figure not shown]
Flow chart. EHL, extended half-life; HAL, Hemophilia Activity List; HJHS, Hemophilia Joint Score; PedHAL, pediatric HAL; PK, pharmacokinetic(s); SHL, standard half-life; VAS, visual analogue scale *Non severe hemophilia patients will be analyzed separately. **In parallel with the prospective study, retrospective data analysis will be performed over a 12 month period prior to inclusion (if no PK profiling has been performed) or from PK profiling prior to inclusion. ***Patients in stratum 2 could undergo PK profiling during SHL prophylaxis as well as during EHL prophylaxis.

Patients/caretakers will fill in the Hemophilia Activities List (HAL) and/or pediatric HAL (PedHAL) before initiation. Moreover, the Hemophilia Joint Health Score (HJHS) will be performed or must have been performed <12 months prior inclusion.

The validated PedHAL/HAL questionnaire and the HJHS are included as clinical parameters to systematically establish baseline values of functional outcome from the patient's perspective and to be informed of joint status, respectively. These clinical parameters may help to evaluate outcomes after implementation of PK guidance.

Furthermore, both patients/caretakers and the treating physician will fill in a specifically developed questionnaire using VAS scales, before the implementation of PK-guided dosing, considering the expectations with PK-guided dosing of prophylaxis. More specifically, in the questionnaire, questions are asked about satisfaction, being informed of factor levels, and expected burden of PK guidance. Moreover, when patients switch to an EHL factor concentrate, the reasons for switching are also asked.

An individual PK profile will be constructed after a factor concentrate dose of 35 to 50 IU/kg, depending on hemophilia type and age of the patient. The frequency and timing of blood sampling during PK profiling is depending on type of hemophilia and type of factor concentrate (
Fig. 2
). No wash out period is required if three prior infusions and time points of infusion are documented. During sampling of the PK profile, laboratory tests will be performed according to
Tables 1
and
2
.

**Table 1 TB210067-1:** Laboratory tests during individual PK profiling for patients with hemophilia A

On FVIII-SHL	Preinfusion	T = 15–30 minute	T = 4 hours	T = 24 hours	T = 48–72 hours	
On FVIII-EHL	Preinfusion	T = 15–30 minute	T = 4 hours	T = 24 hours	T = 48 hours	T = 72–96 hours a
ASAT	X					
ALAT	X					
GGT	X					
LDH	X					
AF	X					
Albumin	X					
Urea	X					
Creatinine	X					
Hemoglobin	X					
Hematocrit	X					
Thrombocytes	X					
Blood group (if unknown)	X					
Factor VIII	X	X	X	X	X	X
VWF:Ag	X	X	X	X	X	X
VWF:Act	X	X	X	X	X	X
VWF:CB	X	X	X	X	X	X
VWFpp	X	X	X	X	X	X
Inhibitor FVIII (only ≥ 18 years)	X					
Bethesda FVIII	X					
Buffycoat	X					
APTT	X	X	X	X	X	X
PT/INR	X					
Factor V	X					
Fibrinogen	X					
Max of 10-mL citrate plasma	X	X	X	X	X	X

Abbreviations: AF, alkaline phosphatase; ALAT, alanine aminotransaminase; APTT, activated partial thromboplastin time; ASAT, aspartate aminotransferase; EHL, extended half-life; FIX, factor IX; FV, factor V; FVIII, factor VIII; GGT, gamma-glutamyltransferase; INR, international normalized ratio; LDH, lactate dehydrogenase; PFA, platelet function assay; PK, pharmacokinetic; PT, prothrombin time; SHL, standard half-life; T, time point; VWF:Act, von Willebrand's factor activity; VWF:Ag, von Willebrand factor antigen; VWF:CB, von Willebrand factor collagen binding; VWFpp, von Willebrand factor propeptide.

a Only in case of an EHL concentrate.

**Table 2 TB210067-2:** Laboratory tests during individual PK profiling for patients with hemophilia B

On FIX-SHL	Preinfusion	T = 15–30 minutes	T = 4 hours	T = 48–56 hours	T = 72–80 hours	
On FIX-EHL	Preinfusion	T = 15–30 minutes	T = 4 hours	T = 24 hours	T = 72–120 hours	T = 168 hours a
ASAT	X					
ALAT	X					
GGT	X					
LDH	X					
AF	X					
Albumin	X					
Urea	X					
Creatinine	X					
Hemoglobin	X					
Hematocrit	X					
Thrombocytes	X					
Blood group (if unknown)	X					
Factor IX	X	X	X	X	X	X
Inhibitor FIX (only ≥ 18 years)	X					
Bethesda FIX	X					
Factor VIII	X					
VWF:Ag	X					
VWF:Act	X					
VWF:CB	X					
VWFpp	X					
Buffy coat	X					
APTT	X	X	X	X	X	X
PT + INR	X					
Factor V	X					
Fibrinogen	X					
Max of 10 mL citrate plasma	X	X	X	X	X	X

Abbreviations: AF, alkaline phosphatase; ALAT, alanine aminotransaminase; APTT, activated partial thromboplastin time; ASAT, aspartate aminotransferase; EHL, extended half-life; FIX, factor IX; FV, factor V; FVIII, factor VIII; GGT, gamma-glutamyltransferase; INR, international normalized ratio; LDH, lactate dehydrogenase; PFA, platelet function assay; PK, pharmacokinetic; PT, prothrombin time; SHL, standard half-life; T, time point; VWF:Act, von Willebrand factor activity; VWF:Ag, von Willebrand factor antigen; VWF:CB, von Willebrand factor collagen binding; VWFpp, von Willebrand factor propeptide.

a Only in case of an EHL concentrate.

**Table 3 TB210067-3:** Laboratory tests during initial PK-guided treatment and follow-up

	Initial PK-guided treatment (12 weeks)			Follow-up treatment under PK guidance (24 weeks)	Bleeds (only when blood sampling is clinically indicated, during total study period)
Visit	1	2	3	1	additional
Hemophilia A					
FVIII	X	X	X	X	X
FIX					X
VWF:Ag					X
VWF:Act					X
VWF:CB					X
VWFpp					X
APTT	X	X	X	X	X
Inhibitor FVIII	X			X	(X)
Max of 10-mL citrate plasma	X	X	X	X	X
Hemophilia B					
FIX	X	X	X	X	X
FVIII					X
VWF:Ag					X
VWF:Act					X
VWF:CB					X
VWFpp					X
APTT	X	X	X	X	X
Inhibitor FIX			X	X	(X)
Max of 10-mL citrate plasma	X	X	X	X	X

Abbreviations: APTT, activated partial thromboplastin time; FIX, factor IX; FVIII, factor VIII; PK, pharmacokinetic; VWF:Act, von Willebrand factor activity; VWF:Ag, von Willebrand factor antigen; VWF:CB, von Willebrand factor collagen binding; VWFpp, von Willebrand factor propeptide.

